## Abstract

**Background:**

Migraine is a leading cause of disability worldwide. Several retrospective studies have suggested that the closure of the Patent Foramen Ovale (PFO) may provide relief from migraines. However, three randomized controlled trials did not meet their primary endpoints regarding migraine cessation, reduction in monthly migraine days, and responder rates.

**Methods:**

The SPRING study is a multicenter, prospective, randomized, and open-label trial designed to compare the effectiveness and safety of PFO closure versus medication in the relief of migraines. The primary endpoint is the total cessation of migraines, as recorded in patient headache diaries during the follow-up period. Additional diagnostic tools include echocardiography with agitated saline contrast, transcranial Doppler, and routine laboratory measurements.

**Conclusion:**

The SPRING trial aims to assess the effectiveness and safety of PFO closure versus medication in mitigating migraines in real-world settings. (Clinical Trails ID: NCT04946734).

## Background

Migraine is recognized the leading cause of disability among individuals under 50, as reported by the World Health Organization's Global Burden of Diseases Study, 2019 [1]. Despite its prevalence, advancements in migraine management have remained relatively stagnant since the 1990s [1]. While effective symptomatic and preventive treatments exist, none can substantially attenuate migraine symptoms. Over the past two decades, numerous studies have indicated an association between migraine risk and the presence of Patent Foramen Ovale (PFO) and its right-left shunt grade, suggesting PFO as a potential causative factor [2–5]. Proposed mechanisms for this correlation include hypoxia, changes in cerebral autonomic regulation, and venous thromboembolism due to right-left shunting and in situ thrombosis within the PFO [6–9]. Furthermore, multiple studies have demonstrated that device closure of PFO may result in migraine relief [10–13]. However, none of the three randomized controlled trials (RCTs) on PFO closure achieved their primary endpoints, including migraine cessation, reduction in monthly migraine days, and responder rates [14–16]. Consequently, current guidelines provide minimal endorsement for PFO closure as a treatment for migraine due to inconsistencies between RCTs and retrospective studies. Recognizing the need for a comprehensive evaluation of PFO closure's efficacy in preventing migraines, we have launched a real-world design RCT. This trial aims to compare the effectiveness and safety of PFO closure versus medication in alleviating migraines.

### Study design

The Spring study is a multicenter, randomized and open-label trail comparing the effectivity and safety of PFO closure vs medicine in alleviating migraine, with a follow-up period of 12 months (ClinicalTrials.gov ID NCT04946734). The trial is performed in 21 centers in China and has been approved by all local ethics committees. Our hypothesis posits that, compared to medication alone (clopidogrel 75 mg q.d. and aspirin 100 mg q.d.), PFO closure accompanied by one months of clopidogrel (75 mg q.d.) and six months of Aspirin (100 mg q.d.) will be more effective in completely ceasing migraines. Patient recruitment is expected to be completed by the end of 2024, with final results anticipated in 2025.

Patients with migraine and PFO were included in this study. Participant inclusion and exclusion criteria are presented in Table 1.

**Table 1 Tab1:** Inclusion and exclusion criteria

Inclusion criteria
1. Subject is aged between 16 and 60 years old.
2. Subject is diagnosed of PFO with right-to-left shunt, confirmed by Transthoracic echocardiography (TTE) or transesophageal echocardiography (TEE) with agitated saline contrast.
3. Subject is diagnosed of right-to-left shunt, confirmed by transcranial doppler with agitated saline contrast.
4. Subject is diagnosed of migraine without identifiable cause of headache.
5. Subject signs an informed Consent Form and is willing to participate in follow-up visits; 6. Primary and secondary endpoints.
Exclusion criteria:
1. Subject is diagnosed of headache with clear etiology.
2. Subject had cerebral hemorrhage, bleeding events in other organs within 3 months or was in high risk of bleeding.
3. Subject presents with ischemic lesions as indicated by brain CT/MR imaging.
4. Subject is diagnosed of hepatic insufficiency: ALT or AST > 3 × ULN at the screening visit.
5. Subject is diagnosed of moderate to severe renal insufficiency: eGFR < 30 ml/min/1.73m2 at the screening visit.
6. Subject has uncontrolled arrhythmia with clinical significance within 90 days.
7. Subject is diagnosed of unstable angina, severe coronary atherosclerosis or myocardial infarction within 90 days.
8. Subject is diagnosed of pulmonary artery embolism, peripheral artery embolism or deep Vein Thrombosis.
9. Subject cannot follow the study procedure due to other acute or chronic diseases.
10. Subject is pregnant or lactating.
11. Subject is under other RCT.
12. Subject has a life expectancy < 1 year.
13. Subject cannot follow the study procedure due to other reasons in the opinion of the investigators.

### Study protocol

The flow chart of the study design is presented in Fig. 1. Once patients are diagnosed with migraine and PFO, a right-to-left shunt is evaluated using transcranial Doppler (TCD) and transthoracic/transesophageal echocardiography (TTE/TEE) with agitated saline contrast. Upon confirmation of the shunt and PFO, investigators will detail the study protocol to the patients. Following their agreement and the signing of the consent form, we will collect routine laboratory test results, brain imaging (CT/MR), rating scale questionnaires, and other baseline characteristics.

**Fig. 1 Fig1:**
[figure not shown]
Flow chart of the study design. This figure explains the flow chart of the inclusion criteria screening and randomization

After a comprehensive review of inclusion and exclusion criteria, the investigators will proceed with the randomization and distribute headache diaries. Patients in the control group will be prescribed aspirin (100 mg daily) for 6 months and clopidogrel (75 mg daily) for 1 month. In contrast, patients in the treatment group will undergo percutaneous PFO closure in the catheterization laboratory.

### PFO device closure

After local anesthesia, a 6-French MPA 2 catheter was inserted into the right heart system through the right femoral vein by placement of a 6-French vascular sheath. Under fluoroscopy, we measured the pressure in right atrium and pulmonary artery to exclude pulmonary hypertension related PFO. Then, we advanced the catheter through the PFO and anchor in the left inferior pulmonary vein. After accessing the size and location of the PFO, the MPA 2 catheter was exchanged for an 8-French or 9-French delivery sheath and a PFO closure device would be placed across the atrium septum under bedside TTE and fluoroscopy. After successful implement, patients were prescribed same medication of Aspirin 100 mg qd for 6 months and clopidogrel 75 mg qd for 1 month, and would be usually discharged home in the next day.

The success of the percutaneous PFO closure procedure will be defined as implantation of the PFO device without any major complication including death, stroke, or any complication that requires surgical or endovascular treatment.

### Follow up

Follow-up assessments will be conducted at 1, 3, 6, and 12 months post-intervention. These will include the recording of migraine diaries, completion of questionnaires assessing migraine impact, quality of life, medication history, and any serious adverse events. At the 6 and 12-month marks, or upon reaching the primary endpoint, additional follow-up assessments will be conducted. These will consist of TTE/TEE with right heart contrast and TCD with a bubble test to re-evaluate the right-to-left shunt. When adverse events are identified during follow-up, investigators will assess the condition and severity to determine whether to terminate the trial.

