### Study outcomes

Primary and secondary endpoints are presents in Table 2. The outcomes of the migraine changes are adjudicated based on the headache diary data. The total days of migraine is defined as migraine frequency per month plus migraine average duration, divided by 24, round up to nearest integral. The definition of responder rate is the percentage of patients who have at least 50% reduction of monthly migraine attacks from their baseline. Other efficacy measures include migraine severity, as assessed by the HIT-6 scale [17], and quality of life alterations, determined by the SF-36v2 questionnaire [18]. These changes would be also analyzed the relationship with a successful PFO closure and residual shunt.

**Table 2 Tab2:** Primary and secondary endpoints

Primary endpoint
Complete cessation of migraine during the follow up.
Secondary efficacy endpoints
Mean reduction of monthly migraine attacks. Mean reduction of monthly migraine days. Responder rate.
Secondary safety endpoints
All-cause mortality. Peripheral embolism. New-onset arrhythmia warranting intervention. New-onset myocardial infarction. Other complications related to PFO closure procedure, device and antiplatelet drugs. Other side effects associated with the drugs used in the study.

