### Data management and monitoring

All clinical data will be de-identified and stored in an electronic data capture system. The Headache Diary Review Committee, blinded to the randomization, will oversee the calculation and recording of migraine severity and frequency. The Independent Event Committee and the Data Safety Monitoring Board will ensure the integrity of the data and monitor the safety of the participants.

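### The visit schedule names only serious adverse events as safety data, while two Table 2 safety endpoints carry no seriousness limit

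*Protocol article*

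**What the plan says.** In the protocol article, the Follow up section sets the timetable: "Follow-up assessments will be conducted at 1, 3, 6, and 12 months post-intervention". It introduces the content of those visits with "These will include the recording of migraine diaries" and continues with "completion of questionnaires assessing migraine impact, quality of life, medication history, and any serious adverse events". The same section ends with a more general sentence: "When adverse events are identified during follow-up, investigators will assess the condition and severity to determine whether to terminate the trial".

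Table 2, under Study outcomes, lists six secondary safety endpoints. Four are specific: death, peripheral embolism, arrhythmia needing intervention, and myocardial infarction. The other two are residual categories: "Other complications related to PFO closure procedure, device and antiplatelet drugs" and "Other side effects associated with the drugs used in the study". Neither has a seriousness threshold.

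Under Data management and monitoring, the article adds: "The Independent Event Committee and the Data Safety Monitoring Board will ensure the integrity of the data and monitor the safety of the participants". It gives no rule there for how events are collected.

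**The concern.** A safety endpoint can be analysed only to the extent that its events are elicited and written down. Here the printed collection scope is narrower than the printed endpoint scope. The difference comes from two explicit statements, not from silence: the authors chose the qualifier *serious* for the visits and put no such qualifier on the two residual rows of Table 2.

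This matters because safety is a stated aim alongside effectiveness, and because the trial is open-label. Closure patients have a catheter procedure and usually go home the next day, so staff observe them directly. For control patients the article describes a prescription and no comparable period of observation. If recording of non-serious events depends on being noticed, and not on a common question put to everyone, the chance of being recorded may not be equal in the two arms.

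**Working it through.** There is no figure in the plan to reproduce. The check sets the statements side by side.

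1. **Named collection at visits (Follow up).** Diaries, questionnaires, medication history, serious adverse events. Safety content: serious events.
2. **Specific endpoints (Table 2, four of six rows).** Death, peripheral embolism, arrhythmia needing intervention, myocardial infarction. Death and myocardial infarction would ordinarily be reported as serious. None of the four rows is in question here.
3. **Residual endpoints (Table 2, two of six rows).** Complications of the procedure, device and antiplatelet drugs, and side effects of the study drugs. With no threshold they cover serious and non-serious events alike. The non-serious part has no matching item in step 1.
4. **Does the closing sentence of Follow up fill the gap?** It speaks of adverse events in general, which is wider than step 1. But it takes effect only once an event has been identified, and its stated purpose is a decision about termination. It creates no duty to ask about non-serious events or to record them as endpoint data.
5. **Do the committees fill the gap?** They can review only what sites report, and the article attaches no collection rule to them.

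**What can be said about size.** Let s be the share of qualifying events that are serious, and d the share of non-serious events recorded anyway because someone notices them. Assume that all serious events are recorded. Then

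captured share = s + (1 − s) × d.

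If d = 0, the captured share is s and the missed share is 1 − s. The article gives neither s nor d, so the missed share could lie anywhere from 0 to 100%.

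**What can be said about the comparison between arms.** Suppose the true event rate R and the share s are the same in both arms, and d differs (d1 with closure, d0 with control). The recorded difference is then

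R × [s + (1 − s) × d1] − R × [s + (1 − s) × d0] = R × (1 − s) × (d1 − d0).

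This is zero if d1 = d0 and non-zero otherwise (when R > 0 and s < 1). Unequal noticing could therefore produce a difference where none exists. Equal noticing would not, although with the same s and d in both arms it would shrink a real risk difference by the factor s + (1 − s) × d. The argument applies to drug side effects, since the article's account of treatment prescribes aspirin and clopidogrel in both arms. Procedure and device complications arise only with closure, so for them the risk concerns the absolute count and not a between-arm contrast.

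**The case against.** The strongest reply is that the visit list is worded inclusively. It says what visits include, whereas the sentence on the repeat shunt tests uses a closed form, so the authors could have closed this list and did not. The last sentence of the section also refers to adverse events without restriction, so non-serious events are expected to come to notice. In addition, an article condenses a fuller protocol, and the full protocol or case report form may well collect every adverse event. Finally, both arms share one visit schedule, so a gap in recording drug side effects would fall on both.

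Much of this stands, and it rules out several stronger readings that a reader might infer:

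- *That visits record serious events and nothing else.* The text does not say so; it names only serious events.
- *That Table 2 specifies non-serious events.* It does not; it sets no limit.
- *That these endpoints will be under-counted, or mostly missed.* This is a risk that depends on how sites apply the text. No rate supports a stronger statement.
- *That the safety comparison is biased by arm.* Different detection is plausible in an open-label trial but is not shown.
- *That drug reactions will be counted twice.* The only study drugs named are aspirin and clopidogrel, so one reaction could fit both residual rows. But both rows are worded as remainders, and no total is described in which an event would count twice. This is a drafting point.

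What the reply does not remove is the mismatch itself. Allowance for condensation excuses what the article leaves out. It does not reconcile two statements that it prints with different scope.

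**Conclusion.** The point holds as a mismatch of scope. Serious adverse events are the only safety data named for the scheduled visits, while two of the six safety endpoints in Table 2 have no seriousness limit. Read as printed, the plan gives no systematic capture of the non-serious events belonging to those two endpoints, and such capture as occurs could differ by arm.

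The size is unknown. The affected endpoint on drug side effects concerns both arms of the planned 440 patients (220 + 220), but the article gives no event rate and no serious/non-serious split. The conclusion assumes that sites take the visit description at face value. If the full protocol already collects all adverse events at every visit, only the wording of the article needs correcting. The matter is worth settling because safety is a stated aim and the change is cheap.

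**What to change.** In Follow up, replace the reference to serious adverse events with all adverse events that bear on the Table 2 safety endpoints. State that these are asked about and recorded at each of the 1, 3, 6 and 12 month visits, with the same questions in both arms, and that seriousness and relatedness are recorded as attributes of each event and do not act as a filter on entry. If the full protocol already does this, the article should say so.

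Optionally, reword the two residual rows of Table 2 so that a reaction to an antiplatelet drug belongs to only one of them, for example one row for procedure and device complications and one for drug-related effects.

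The cost is a slightly longer visit and case report form. No visit or procedure is added, and treatment is unaffected.

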### Study outcomes

Primary and secondary endpoints are presents in Table 2. The outcomes of the migraine changes are adjudicated based on the headache diary data. The total days of migraine is defined as migraine frequency per month plus migraine average duration, divided by 24, round up to nearest integral. The definition of responder rate is the percentage of patients who have at least 50% reduction of monthly migraine attacks from their baseline. Other efficacy measures include migraine severity, as assessed by the HIT-6 scale [17], and quality of life alterations, determined by the SF-36v2 questionnaire [18]. These changes would be also analyzed the relationship with a successful PFO closure and residual shunt.

**Table 2 Tab2:** Primary and secondary endpoints

Primary endpoint
Complete cessation of migraine during the follow up.
Secondary efficacy endpoints
Mean reduction of monthly migraine attacks. Mean reduction of monthly migraine days. Responder rate.
Secondary safety endpoints
All-cause mortality. Peripheral embolism. New-onset arrhythmia warranting intervention. New-onset myocardial infarction. Other complications related to PFO closure procedure, device and antiplatelet drugs. Other side effects associated with the drugs used in the study.

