### Sample size and statistical considerations

This was a randomized controlled study with PFO blocking group as the intervention group and drug treatment group as the control group. Migraine frequency (monthly migraine days), improvement in migraine frequency, severity (migraine scale score) and quality of life score were the outcome indicators. According to previous reports, the frequency of migraines treated with medication was 6.5 ± 2.4 days/month. The migraine HIT-6 score was 66.2 ± 5.1; After treatment, the number of migraine attacks per month can be reduced by 25%; SF12 quality of life score increased by 1.2 ± 6.9 points after treatment. The frequency of migraine was expected to decrease by 0.6 days in PFO occlusion group. Migraine scale HIT-6 score decreased by 1.5 points; After treatment, the number of migraine attacks per month can be reduced by 50%; SF12 quality of life score improved by 4.2 points after treatment. The test level was set as bilateral α = 0.05, and the assurance was 80%. PASS 15.0 software was used to calculate the required sample size of 113, 183, 60 and 156 cases in each group based on the above four observation indicators. Taking the maximum sample size and considering 20% of the cases of loss and refusal to visit, the final requirement was 220 cases in the PFO blocking group and 220 cases in the drug treatment group.

The primary endpoints will be analyzed across different analysis sets: Intention-to-Treat, per-protocol, and as-treated, with the primary analysis set being Intention-to-Treat. Categorical variables will be described using rates and composition ratios. Group differences in variables such as migraine termination, sociodemographic factors, migraine incidence rate, changes in migraine characteristics (with or without aura and their changes), effective closure rates, or residual leakage will be compared using the chi-square test. Continuous variables will be characterized based on their data distribution, utilizing means, standard deviations, medians, and interquartile ranges. Group differences in variables such as sociodemographic factors, severity and frequency of migraine attacks, and quality of life scores derived from the SF-36v2 questionnaire will be compared using t-tests or the Wilcoxon test.

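### The stated rule for migraine days adds an attack count to a duration, so no reading of it counts days with migraine; one secondary efficacy endpoint is affected

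*Protocol article*

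**What the plan says.** Study outcomes gives one operational rule for total migraine days: "migraine frequency per month plus migraine average duration, divided by 24, round up to nearest integral". No unit is named for the duration; the division by 24 implies hours. Table 2 lists "Mean reduction of monthly migraine days" as a secondary efficacy endpoint, next to "Mean reduction of monthly migraine attacks" as a separate one.

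The sample-size section uses migraine days as the first of four planning indicators. It states that, in previous reports, "the frequency of migraines treated with medication was 6.5 ± 2.4 days/month", and that "The frequency of migraine was expected to decrease by 0.6 days in PFO occlusion group". It also uses the word frequency in a second sense: "Migraine frequency (monthly migraine days", whereas in the Study outcomes rule frequency has to mean attacks per month.

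Data management and monitoring gives a blinded diary committee oversight of the calculation of migraine severity and frequency, but supplies no other formula.

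**The concern.** The rule adds two quantities with different units, and dividing by 24 does not turn the sum into days per month. A programmer has to choose where the division applies, or decide that *plus* was meant as *times*. These choices give different variables and different treatment effects from the same diary. If frequency is read as the sample-size section uses it, the rule is also circular, because days become a function of days.

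At stake are the validity of one named efficacy endpoint and its comparability with earlier work. The Discussion sets this trial beside an earlier randomised trial whose primary endpoint was the reduction in monthly migraine days. The trial is open-label, so a choice between readings left until analysis could be made with the arm results in view.

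**Working it through.** **Inputs.** The rule comes from Study outcomes. Let f = attacks per month and d = mean hours per attack. The documents give no attack durations, so d = 4 to 72 h is an assumed range.

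**Three readings, each rounded up**
- A: (f + d)/24, the literal wording
- B: f + d/24, with the division applied to duration only
- C: f × d/24, with *plus* as a slip for *times*

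| f | d (h) | A | B | C |
|---|---|---|---|---|
| 8 | 12 | 20/24 = 0.83 → 1 | 8.5 → 9 | 96/24 = 4 |
| 2 | 12 | 14/24 = 0.58 → 1 | 2.5 → 3 | 24/24 = 1 |
| 6 | 4 | 10/24 = 0.42 → 1 | 6.17 → 7 | 24/24 = 1 |
| 10 | 24 | 34/24 = 1.42 → 2 | 11 | 240/24 = 10 |

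**Same patient, three effects.** For 12-hour attacks falling from 8 to 2 per month, the reduction is 1 − 1 = 0 under A, 9 − 3 = 6 under B and 4 − 1 = 3 under C.

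**Reading A barely responds to attack count.** Halving attacks from 6 to 3 leaves the score unchanged at d = 4, 12, 24, 48 and 72 h (1, 1, 2, 3 and 4, both before and after). Whenever f + d is at most 24, every patient with any migraine scores 1.

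**Reading B repeats the attacks endpoint.** For whole-number f and d above 0 and below 24 h, rounding f + d/24 up gives f + 1. In a patient who still has attacks, the change equals the change in attacks.

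**Reading C has units of days but does not count days.** Six 4-hour attacks on six different days score 1, while a count of days with migraine gives 6.

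**Against the planning figure.** With f = 6.5 attacks per month:

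| d (h) | A | B | C |
|---|---|---|---|
| 4 | 1 | 7 | 2 |
| 12 | 1 | 7 | 4 |
| 24 | 2 | 8 | 7 |
| 48 | 3 | 9 | 13 |

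A value of 6.5 under A needs f + d = 6.5 × 24 = 156. B and C can produce numbers of that size, but those numbers are not counts of migraine days.

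**Does the rule reach the sample size?** The plan states a "required sample size of 113, 183, 60 and 156 cases in each group" and takes the largest. HIT-6 (difference 1.5, SD 5.1, two-sided 0.05, 80% power) gives 2 × (1.960 + 0.842)² × 5.1²/1.5² ≈ 182, or 183 with the t distribution. That matches the stated 183, and 183 × 1.2 = 219.6, rounded up to 220. The stated final number therefore comes from HIT-6.

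The 113 for migraine days does not reproduce: the same formula with 0.6 and 2.4 gives 252. That is a separate sample-size question. The calculation uses the published mean and SD, not the diary rule, so it does not bear on this point.

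**The case against.** The strongest reply is that this is a wording slip in a condensed article. *Plus* was probably meant as *times*, the full protocol is not shown, and the text has other language errors. That is plausible, and the article does not prove that the trial computes days this way. But the rule is stated explicitly, nothing in the article corrects it, and the *times* reading still measures cumulative time rather than days with migraine.

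A reader might infer more than the documents support:

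- **That the endpoint cannot be computed.** Each reading can be calculated from frequency and duration. The fault is that the rule is invalid and ambiguous.
- **That the treatment effect disappears.** This holds only for the literal reading; the other two move from 9 to 3 and from 4 to 1 in the example.
- **That a value near 6.5 is impossible.** Even under the literal reading, one attack of 150 h gives 151/24 = 6.3, rounded up to 7. Ruling this out needs a cap on duration that the documents do not give. The same holds for any claim that nearly all patients would score 1 or 2.
- **That a 0.6-day difference is lost because scores are rounded to whole days.** A difference in group means can be smaller than the step in individual scores. Rounding adds about 1/12 to the variance: √(2.4² + 1/12) ≈ 2.42 against 2.4, which is negligible.
- **That the 6.5 ± 2.4 is wrong because of the rule.** That figure comes from earlier reports and was not produced by this formula. The problem is comparability.

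**Conclusion.** The definition of migraine days is wrong as written and needs correcting. Under each of the three readings, the result is something other than the number of days with migraine, and the readings disagree: the same patient shows a reduction of 0, 6 or 3. The outcome also cannot be set against the 6.5 ± 2.4 days/month used for planning.

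The reach is limited to one secondary efficacy endpoint. Complete cessation, the responder rate (defined on attacks) and the attacks endpoint do not use the rule, and the stated 220 per group follows from HIT-6. The documents give no ground for extending the criticism to the primary analysis.

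The conclusion assumes that duration is in hours. The numerical examples assume attack durations that the documents do not give. The mismatch of units depends on neither.

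**What to change.** Before any analysis by arm, delete the formula and define monthly migraine days as the number of diary days with migraine, standardised to the diary time actually recorded. Confirm that this is the definition behind the 6.5 ± 2.4 days/month in the earlier reports. Use the word frequency in one sense throughout.

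The article does not say whether the diary records the date of each attack. If it does, the cost is a short text change and a small change to endpoint programming.

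If it holds only attack counts and durations, days with migraine may not be recoverable. In that case replace *plus* with *multiplied by*, drop the rounding, and label the variable cumulative migraine time (24-hour equivalents) rather than migraine days. The cost is then larger: the endpoint changes its name and meaning, and it should not be compared with published migraine-day figures.

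### Stroke is a named complication of the procedure but not a named safety endpoint, so non-fatal strokes judged unrelated to treatment enter no listed safety endpoint in either arm

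*Protocol article*

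**What the plan says.** Table 2 (Study outcomes) lists six safety items. Four carry no condition on cause: "All-cause mortality. Peripheral embolism. New-onset arrhythmia warranting intervention. New-onset myocardial infarction". The other two depend on attribution: "Other complications related to PFO closure procedure, device and antiplatelet drugs" and "Other side effects associated with the drugs used in the study". Neither stroke nor TIA appears in the table.

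The only place where the article uses the word stroke is the PFO device closure section. There a successful procedure is an implantation "without any major complication including death, stroke, or any complication that requires surgical or endovascular treatment". That definition can apply only to patients who undergo closure.

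On data collection, the Follow up section states "Follow-up assessments will be conducted at 1, 3, 6, and 12 months post-intervention" and includes in those visits "medication history, and any serious adverse events", with no limit by arm or by cause. The Data management and monitoring section provides an Independent Event Committee and a Data Safety Monitoring Board.

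**The concern.** The trial sets out to compare the safety of two strategies as well as their effectiveness. For that comparison, an event should count by the same rule in both arms. Myocardial infarction and peripheral embolism meet this standard: they count whatever caused them. Stroke does not. It counts in Table 2 only if it is fatal or if someone attributes it to treatment, and the two arms differ in what it can be attributed to.

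Stroke is a poor event to leave to attribution here. The article itself ranks it beside death as a major procedural complication. Its Background also cites clot within the PFO and venous thromboembolism through the shunt among the proposed mechanisms linking PFO to migraine, so an embolic event in a patient whose PFO stays open is plausible on the article's own reasoning. Such an event in the control arm has no obvious place in Table 2 unless it is fatal.

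**Working it through.** There is no figure to reproduce; the check traces how a stroke could enter Table 2.

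**Step 1. Could peripheral embolism include stroke?** The eligibility criteria suggest not. Exclusion criterion 8 reads "Subject is diagnosed of pulmonary artery embolism, peripheral artery embolism or deep Vein Thrombosis". Ischemic brain lesions have their own item (exclusion 3), and cerebral hemorrhage has another (exclusion 2). The article's vocabulary keeps peripheral embolism apart from cerebral events. Even a generous reading would not reach hemorrhagic stroke.

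**Step 2. What can an event be attributed to in each arm?** In the closure arm: the procedure, the device, or the antiplatelet drugs given afterwards. In the control arm: drugs only, since "Patients in the control group will be prescribed aspirin (100 mg daily) for 6 months and clopidogrel (75 mg daily) for 1 month" (Study protocol section, below Fig. 1).

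**Step 3. Routes into Table 2.**

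| Stroke | Closure arm | Control arm |
|---|---|---|
| Fatal | Counted as a death | Counted as a death |
| Non-fatal, attributed to procedure or device | Counted | Cannot arise |
| Non-fatal, attributed to a study drug | Counted | Counted |
| Non-fatal, judged unrelated | No listed safety endpoint | No listed safety endpoint |

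Events in the last row remain on record as serious adverse events, if they meet that definition.

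**Step 4. How the routes differ over time.** By the Study protocol section, the control drugs end at month 6 at the latest, and follow-up runs to month 12. For 12 − 6 = 6 months, half of the follow-up, a control patient is on no study drug to which a new stroke could naturally be attributed, while a closure patient still carries the device. The Study design section names the control drugs without a duration, so this step rests on the Study protocol section.

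**Step 5. Direction.** Suppose both arms had the same number of non-fatal spontaneous strokes. Some in the closure arm might be ascribed to the device and counted; none in the control arm could be. That tilts the count against closure. The opposite error is also possible: a device-related stroke wrongly called unrelated drops out of Table 2 altogether. The documents do not allow the net direction to be settled.

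**The case against.** The strongest reply is that the events are not lost. Fatal strokes count under all-cause mortality whatever the cause. Serious adverse events are recorded at every visit in both arms, and two bodies oversee safety. Nothing confines the safety comparison to Table 2, and a tabulation of serious adverse events by arm is the kind of detail a condensed article leaves to the full protocol or the SAP. This stands. A reader might infer that control-arm strokes not blamed on a drug can never enter the safety comparison; the documents do not support that. What they support is narrower: such strokes, if non-fatal, are in no listed safety endpoint. The same is true of closure-arm strokes judged unrelated.

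A reader might also infer that relatedness is judged by people who know the treatment arm. Treatment is open-label, and blinding is stated only for the Headache Diary Review Committee, but the article does not say who judges relatedness or whether they are blinded. The risk is open; it is not a documented fact.

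It is also fair to say that procedural and device complications can occur only where there is a procedure and a device, so counting them in one arm is not in itself a bias. The difficulty is that for stroke there is no cause-neutral count beside them, as there is for myocardial infarction.

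Finally, it may be tempting to extend the point to bleeding. That does not follow. Both arms are prescribed the same antiplatelet course in the Study protocol and PFO device closure sections, and both attribution-based items in Table 2 admit drug-related bleeding in either arm.

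**Conclusion.** The point holds as a gap in the list of safety endpoints. Stroke is treated as major in the definition of procedural success and is not named in Table 2. Non-fatal strokes judged unrelated to treatment therefore reach no listed safety endpoint in either arm, and the control arm is the more exposed because it has one route to attribution where the closure arm has three.

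No size can be put on it. The article gives no stroke rate. A reader might multiply the planned 220 patients per arm by an assumed rate, but the product would only be an upper bound on the omitted control-arm events: fatal and drug-attributed strokes are counted, and the 220 already allows for 20% loss. The finding does not depend on any count.

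The conclusion rests on two readings: that peripheral embolism excludes cerebral events, as the exclusion criteria suggest, and that Table 2 is the full list of safety endpoints. It concerns secondary safety endpoints only and leaves the primary endpoint and the power calculation untouched. It is an inexpensive improvement to the safety comparison.

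**What to change.** Add stroke and TIA to the safety endpoints in Table 2, with ischemic and hemorrhagic stroke both included. Count them in both arms from randomisation to month 12 regardless of judged relatedness, with adjudication by the existing Independent Event Committee. Keep the items on treatment-related complications as descriptive. Since visits are timed from the intervention, state that the counting window opens at randomisation and how month 12 is fixed in each arm.

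The cost is mainly table wording. Strokes that qualify as serious are already collected at 1, 3, 6 and 12 months, and the committee is already in place. A TIA may not always meet the definition of a serious adverse event, so the visit form should ask for it by name.
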